### Procedure

A standardised data-collection protocol was implemented to ensure methodological consistency across study sites. All assessment instruments have demonstrated strong psychometric properties and are validated in prior research.

The project entails two main study phases: baseline and follow-up (see figure 1). During baseline, participants will undergo an extensive clinical assessment including interviews, self- and parent-ratings, self-control and intelligence testing, and electrocardiogram (ECG). Further, they will participate in an ‘in-situ’ assessment. In this part, the participant will be in a situation eliciting frustration (mimicking irritability) while various emotional, cognitive and psychophysiological parameters (i.e., ECG) will be examined. The clinical and ‘in-situ’ assessments will be conducted in one appointment. Participants will then conduct 2 weeks of EMA, consisting of ESM, an ambulatory cognitive task, ambulatory heart rate measurement and actigraphy, as well as passive smartphone sensing (for those using their own smartphone). Finally, participants and their caregivers will be reassessed at a 1-year follow-up. Given the intensive, multimodal nature of our protocol, a 1-year interval offers the optimal balance between capturing meaningful developmental changes in irritability-related psychopathology and maintaining feasibility, retention and ethical acceptability, consistent with current youth mental-health and early-risk-prediction studies. The 1-year follow-up assessment will include a clinical re-assessment of tonic and phasic irritability (see Measures section for details), general psychopathology, severity of psychopathology, global functioning, significant life events and treatment or help-seeking behaviours. Financial compensation will be provided in the form of vouchers to avoid direct monetary compensation that might be used inappropriately (e.g., cigarettes, alcohol or illegal substances).

**Figure 1 F1:**
[figure not shown]
Study overview. Ecological momentary assessment (EMA) phase follows baseline assessment directly and includes ESM self-report and parent-report, as well as cognitive control task (hand holding smartphone symbol), ambulatory autonomic function using a wearable (wearable symbol) as well as passive smartphone sensing (smartphone wifi symbol). ‘In-situ’: situation mimicking daily life situation generating frustration. EMA, ecological momentary assessment; ESM, experience sampling method; HRV, heart rate variability.ECG:electrocardiogram

### Measures

#### Baseline assessment

Interview and questionnaire data are collected via REDCap (Research Electronic Data Capture). Self-report measures are completed directly by the participants themselves either at home (before the first lab assessment) or at the lab during the assessment. For children aged 8–10 years, questionnaires can be completed with the support of a parent or the research team.

Demographic variables include age, sex, gender, pubertal stage, ethnicity, school form, chronic illnesses, medication intake, visual acuity and therapeutic follow-up. Psychosocial variables include socioeconomic status, family composition and marriage status of parents. Physical activity, sleep, traumatic events and screen use will also be assessed.

Psychiatric diagnoses will be obtained using the clinical interview Kiddie Schedule for Affective Disorders and Schizophrenia.^78^ Severity of psychopathology (Clinical Global Impression Scale^79^ and global functioning Children’s Global Assessment Scale^80^) will be assessed by the interviewer.

Irritability will be assessed comprehensively using the Affective Reactivity Index^81^; the Child Behavior Check List (for parents and young children—8–10 years old)/Youth Self-Report (for youths from 11 to 14 years old)^82^; and a questionnaire specifically developed to measure phasic and tonic components of irritability (the Tonic and Phasic Irritability Scale).^32^

The short version of the Difficulties in Emotion Regulation Scale^83^ and the Diagnostic Tool for Affective Dysregulation in Children–Screening Questionnaire^84^ will be used to assess emotion regulation problems (also rated by the parent). The Brief Self-Control Scale^85^ will quantify general trait self-control. The Anger Rumination Scale^86^ will assess the rumination (i.e., unwanted thoughts, emotions) related to past events eliciting anger. Regarding sleep quality, chronotype will be assessed with the Morningness-Eveningness Scale for Children^87^ and daytime sleepiness with the Epworth sleepiness scale adapted for children and adolescents.^88^ Adverse childhood events will be measured with the Adverse Childhood Experiences scale.^89^ Detailed information about routine clinical care will additionally be collected during the whole study phase.

The Symptom Checklist-90-R^90^ will measure psychopathological symptoms of parents. The Brief Irritability Test^91^ will measure parents’ irritability and the Tonic and Phasic Irritability scale^32^ will measure children’s irritability. The short version (20 items) of the Parental Affect Test^92^ will evaluate how parents deal with negative situations with their children. The short version of Being a Parent Scale^93^ will assess measures of parenting satisfaction and efficacy. The short version (28 items) of the Parenting Styles and Dimensions Questionnaire^94^ will measure the three parenting styles, namely authoritative, authoritarian and permissive parenting. The Parent-Child Coercive Process Scale^95^ measures coercive processes in parent-child dyads.

General intelligence will be assessed with the five subtests Vocabulary, Block Design, Figure Weights, Digit Span and Coding of the Wechsler Intelligence Scale for Children-Fifth Edition^96^ as this short version has been demonstrated to provide an accurate estimation of general intelligence.^97^

*Cognitive control* will be assessed with an SST.^98 99^ The SST will consist of performing a choice reaction while restraining from responding when facing a stop signal. Patients must decide if the face presented is male or female by pressing one of two response keys. Stimuli consist of neutral and angry facial expressions from 12 individuals (6 females and 6 males; Macbrain Face Stimulus Set, www.macbrain.org). The stop signal consists of a red square appearing around the faces after a delay (initially set at 250 ms) that is adjusted depending on the participant’s success in inhibiting responses in the preceding stop trials. In cases of successful response inhibition, delay increases, and in cases of failed response, delay decreases for the next stop trial. This adjustment is supposed to result in a mean success rate for stop trials of about 50%, allowing for a good assessment of the stop-signal reaction time (SSRT).^100^ Presentation will be randomised across participants to avoid practice effects due to the repetition of the presentation of the stimuli. Three main scores will be computed: SSRT (time during which the inhibition of an already initiated response is possible), proactive adjustments (slowed: cautious; speeded: risky) and reactive adjustments (error-monitoring). An analogous task (i.e., go/no-go) will repeatedly be used during the EMA phase (see Ecological momentary assessment section).

During the *delay discounting* task, children choose between a varying amount of hypothetical money now or a hypothetical 100 CHF after a varying delay. The immediate money varies from 0 to 100 CHF in 5 CHF increments. The delayed money (always 100 CHF) is available after one of four delays (now, in 7, 30 or 365 days). Choices will be randomly displayed on the right and left sides of the screen. Three additional questions will be used to assess attention to the task (100 CHF in X days vs 100, 95 and 90 CHF now). For each of the delays, a double-limit algorithm adjusts the immediate reward based on previous choices in order to narrow the range of values. It then converges into a so-called indifference value, which the subject considers to be equivalent to the delayed reward.^101^ Reward is typically discounted in a hyperbolic function that depends on the amount, delay and a free impulsiveness indicator *k*. This variable *k* is the main dependent task variable, which can be obtained by fitting a hyperbolic function to the indifference values for every delay. Larger *k* values imply greater reward devaluation. The task has been found to be feasible and valid in 7–9-year-old children.^102^

#### Psychophysiological measures

HRV will be measured during a 5 min baseline while patients complete a minimally demanding Color Detection Task (CDT).^103^ ECG will be recorded using an EcgMove4 sensor (movisens GmbH, Karlsruhe, Germany) attached to the participants’ chest at the base of the sternum using a flexible belt with two integrated electrodes. ECG signals will be recorded at a sampling rate of 1024 Hz. Reporting of HRV processing and analyses will adhere to the Guidelines for Reporting Articles on Psychiatry and HRV.^104^ After visual inspection, data will be processed in Kubios HRV 3.0 Premium, including manual correction of R-peak detection and artefact removal. The square root of the mean squared difference of successive inter-beat-intervals (RMSSD, in ms) will be calculated for each patient as a time-domain measure of vagal activity.^105^

#### In-situ assessment

The ‘In-situ’ assessment of frustrative non-reward will be conducted using a rigged Affective Posner Task.^62106^,^109^ Participants are asked to identify a target following a cue by button press (left or right). The task consists of three conditions differing in the feedback participants receive. In the first condition, participants receive feedback regarding the accuracy of their performance on each trial. In the second condition, participants win or lose monetary incentives based on their performance. In the third condition, feedback is manipulated: participants receive rigged feedback in about 60% of trials and accurate feedback in about 40% of the correct trials. On trials with rigged feedback, participants are informed that they were ‘too slow’ and lose money regardless of their actual reaction time. In all three conditions, auditory and visual feedback are provided depending on the participant’s response. Delta of accuracy between blocks will index impairment of cognitive control due to affective context. Self-perceived frustration tolerance will be measured at the end of the task.^110^ Subjective feelings throughout the task will be measured with items from the brief Positive and Negative Affect Schedule (PANAS).^111 112^ ECG measurement will be continued during the ‘in-situ’ assessment. At the end of the task, a recovery phase is introduced through the administration of the CDT cited earlier. Self-perceived frustration tolerance will be measured during the task with a short version (i.e., irritated, nervous, attentive, agitated, angry) of the PANAS.^111 112^

#### Ecological momentary assessment

The EMA includes four types of measures: ESM (i.e., self-report), ambulatory cognitive assessment, autonomic regulation as well as passive monitoring.

ESM will be prompted four times a day (morning, noon, afternoon and evening). Reminders will be sent two times for each prompt after 30 and 60 min. Those children who do not own a smartphone will respond to ESM on their parents’ smartphone. All participants will respond during 14 consecutive days (during school period, not holidays). The ESM encompasses items measuring context, location, sleep, affect (current and since the last prompt), aggression, violent ideations, anger rumination, self-control, tonic as well as phasic irritability and conflicts. Parents will answer questions regarding their children but also their own affect, self-control and interaction with their child (current and since the last prompt).

An event-related questionnaire will be sent each morning to parents in case they would like to individually report a child’s temper tantrum during any given moment of the day. This questionnaire can be filled out multiple times during the day.

To collect the cognitive ambulatory assessment, participants will perform the online go/no-go task (in line with the lab version^113^ two times a day (coupled with the morning and afternoon assessments), provided through Inquisit 6 (a software for administering psychological tests that gives the option of running tests online) and already used successfully in a previous study.^114^

Ambulatory autonomic regulation will be assessed using a wristband (i.e., Garmin vívosmart 5), during the whole EMA period (14 days). Inter-beat intervals (time between two successive pulse pressure waves) are obtained using PPG (photoplethysmography). Each heartbeat will be detected individually; furthermore, each beat will be accompanied by a binary confidence metric (high=1, low=0) indicating the measurement’s quality. PPG data will be preprocessed using Firstbeat analysis software to calculate RMSSD in 1-minute intervals. The Labfront and Garmin Connect apps will be installed on the youth’s or the parent’s smartphone during the baseline assessment, to enable data extraction at the end of the EMA period. Moreover, the Ethica Avicenna application (also installed on the participants’ smartphone) will record screen state, Bluetooth and app usage (only on Android). To approximate app usage in participants owning an iPhone, we will additionally prompt those participants to send screenshots of their screen time app covering the 2 weeks of the EMA.

To maximise EMA response compliance, we will monitor daily REDCap entries. Additionally, every 2 or 3 days, we will review the synchronisation status for both mobile applications (i.e., Labfront, Garmin Connect). Participants will receive an SMS reminder on their smartphone if a decline in compliance is detected. If compliance does not improve, a member of the research team will contact the participant by phone to identify potential difficulties, offer support and encourage re-engagement during this phase.

#### Follow-up assessment

The follow-up assessment will take place 1 year after the baseline assessment. The clinical assessment will be similar to the baseline and contain the same measures of tonic and phasic irritability, psychopathology, severity of psychopathology and global functioning. In addition, we will monitor whether participants received any form of therapy or no therapy at all. All significant life events that potentially happened between assessments will also be queried. Table 2 summarises all measures.

**Table 2 T2:** Overview of the assessments

Assessment	Baseline		Ecological momentary assessment		Follow-up
Mode	Lab (+ remote)		Remote, 2–4 times a day		Lab
Participant (parent/child/both)	Child	Parent	Child	Parent	Both
Duration	3–3.5 hours	2.5–3 hours	3–6 min	3 min	2 hours
Instruments					
Sociodemographics	+	+			
Psychiatric diagnoses	+	+			+
Severity of psychopathology and global functioning	+				+
Emotional and behavioural problems	+	+			+
Emotion regulation	+				
Tonic and phasic irritability	+	+			+
Anger rumination	+	+			
Self-control	+	+			
Sleep	+				
Parental dimensions		+			
General intelligence	+				
Cognitive control	+				
In situ frustration (including ECG)	+				
Experience sampling			+	+	
Ambulatory cognitive control			+		
Ambulatory HRV			+		
Passive sensing			+		

ECG, Electrocardiogram; HRV, heart rate variability.

### Statistical analysis plan

We will assess cross-language measurement invariance (French vs German) for multi-item scales using multi-group confirmatory factor analysis, testing configural, metric and scalar (threshold) invariance based on model fit and Δcomparative fit index (CFI)/Δroot mean square error of approximation (RMSEA). If inter-site differences are detected, the site will be included as a covariate in the statistical models to control for potential confounding.

#### Aim 1

First, we will compute separate standardised composite scores for tonic and phasic irritability at the within- (from the ESM measures) and between-person level (from the interviews and questionnaires). To assess convergent validity, multilevel regression models will then be used to test for associations between the tonic irritability composite score from ESM measures and the tonic irritability composite score from the clinical measures. The same models will be computed for phasic irritability. To test our second hypothesis, we will compute a lagged logistic multilevel regression model where tonic irritability from one ESM sampling will predict the presence of phasic irritability (categorical score) in the next ESM sampling (within-person level). Finally, to investigate the role of the psychosocial context (including parenting), multilevel regression analyses will be used to assess the role of conflict and psychosocial context on tonic/phasic irritability at the within-person level.

#### Aim 2

To test the pathophysiological correlates of tonic and phasic irritability, we will compute a multivariate linear mixed model,^115^ which represents a statistical framework for analysing fixed and random effects on multiple outcomes (i.e., tonic vs phasic irritability).^116^ This approach enables us to compare the effects of the pathophysiological variables on tonic versus phasic irritability, which are two separate but correlated outcomes. The model will hence allow computing effect sizes that will be compared with assessing the common and unique pathophysiological correlates (i.e., ambulatory cognitive control, ‘in-situ’ HRV) of tonic and phasic irritability both at a within- and between-person level. Lagged multilevel regression models will further be used to assess the temporal dynamics of the pathophysiological (e.g., ambulatory HRV, actigraphy and cognitive control) correlates of tonic and phasic irritability at the within-person level.

#### Aim 3

Finally, to understand the role of tonic and phasic irritability in psychopathology, two approaches will be used. First, we will adopt a dimensional perspective and use the severity of psychopathology of internalising and externalising problems (as the outcome variables at the between-person level). We, thus, must reduce the ESM measures to single measures for each participant. To do so, we will compute the mean and RMSSD that will be used in hierarchical regression analyses, also including the measure of irritability from clinical (or baseline) assessment. As both dimensions of irritability will be correlated and thus share a great part of common variance, we will compute the unstandardised residuals from regression analyses (tonic irritability regressed on phasic irritability and conversely).^117^ These scores will be used in the following regression models in order to calculate the independent importance of one dimension of irritability in understanding the severity of psychopathology. Second, we will adopt a transdiagnostic approach and use multilevel regression analyses (i.e., means-as-outcomes models)^118^ as proposed in the only previous paper combining within- and between-person approaches^51^ to assess the differences in ambulatory tonic and phasic irritability (within-person level) across diagnoses (between-person; e.g., anxiety, depression, DMDD, ADHD and oppositional defiant disorder).

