## Methods and analysis

This research project employs a longitudinal design combining observational and experimental elements. The project is a multi-centre study including two sites: (a) the Division of Child and Adolescent Psychiatry at the University Hospital of Lausanne and (b) the Division of Youth Mental Health at the Faculty of Psychology at the University of Basel. The data collection phase begins in January 2025 and will last until the end of 2027.

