### Participants

We will recruit n=180 youths who are currently seeking help from various child and adolescent mental health services (as well as those who have sought help in the past 12 months). Moreover, we will recruit n=40 healthy children (i.e., not seeking help and no diagnosed psychiatric disorder). In addition, we will recruit participants’ parents (n=220–440). Thus, the total sample of the study will range from 440 to 660. Table 1 describes the inclusion and exclusion criteria. The sample size of a total of n=220 children was justified by a power calculation (see power calculation section).

**Table 1 T1:** Inclusion/exclusion criteria for children and their legal guardians

Criteria	Children	Legal guardian
Inclusion		
Being aged 8–14 years	x	
Having sufficient intellectual abilities and sufficient language skills (German or French) to be able to participate in the study	x	x
Drug naïve (no psychotropic medication, no medication impacting heart rate)*	x	
Written informed assent or written informed consent	x	x
Exclusion		
Known cardiovascular disorders impacting the heart functioning, severe health conditions that currently demand intensive medical treatment (i.e., cancer, neurological disease, severe conditions related to mental health)	x	
Having a pacemaker	x	
Known diagnoses in schizophrenia or psychosis spectrum as well as in autism spectrum disorders at study inclusion	x	
Known active life crisis (i.e., intense suicidal ideas or behaviours)	x	

* As we aim to characterise the associations between these phenomena without the confounding influence of medication that may alter emotional, behavioural and psychophysiological functioning.

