#### Power analyses

We approximated the power of the main analyses (i.e., the multilevel regression) by using Monte-Carlo simulation (n=1000 repetitions). Based on pilot studies (unpublished data), we assumed a correlation coefficient of r=0.75 between repeated measures, participant compliance of 82% and an additional dropout of 20%. For the concurrent model, 56 repeated measures for each participant (4× measure a day for 14 days) will be collected for n=220 participants. For the temporal model (or lagged model, predicting next measures), 42 measures (three lagged variables per day for 14 days) will be available for the 220 participants. We expect a correlation between tonic and phasic irritability of r=0.60.^35^ The approximated power of these analyses focuses on the effects of β_n_ (between-person level) and γ_n_ (within-person level) for the repeated measures. These models have a power of 0.99 to detect small effect sizes at the within-person level and a power of 0.94 to detect medium effect sizes at the between-person level. For the temporal model (lagged model), we will achieve a power of 0.91 to detect small effect sizes at the within-person level and a power of 0.82 to detect medium effect sizes at the between-person level.

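### Site is adjusted for only if a difference between sites is detected, with no criterion given; it should be a prespecified covariate in every model that estimates a between-person effect

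*Protocol article*

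**What the plan says.** The study runs in Lausanne and Basel: "The project is a multi-centre study including two sites" (Methods and analysis). Table 1 requires "sufficient language skills (German or French) to be able to participate in the study".

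The Statistical analysis plan section opens with a language check, "We will assess cross-language measurement invariance (French vs German) for multi-item scales using multi-group confirmatory factor analysis", judged by model fit and by changes in CFI and RMSEA. The next sentence is the rule at issue: "If inter-site differences are detected, the site will be included as a covariate in the statistical models to control for potential confounding". The article does not say what counts as detection, which variables are compared, or whether one decision governs all models. No model described under Aims 1 to 3 names site unconditionally.

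The Procedure section says that data collection is standardised across sites. The Dissemination section plans preregistration of the main analyses, so the rule can still be settled.

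**The concern.** Whether a confounder matters does not turn on whether a preliminary comparison flags it. With two sites and at most 220 children, failure to detect a moderate site difference is weak evidence that there is none. If site shifts both a predictor and an outcome and is left out, part of the site difference appears as an association between the two. The model finally fitted also depends on the data, while its standard errors are reported as if it had been fixed in advance.

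The results at stake are the between-person ones: convergent validity in Aim 1, the between-person correlates in Aim 2, and the regressions and diagnosis comparisons in Aim 3.

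**Working it through.** **The plan's own figure.** There is none for detecting a site difference. The nearest is the power of 0.94 for a medium between-person effect. The article gives no numerical effect size, alpha or model variances, so that figure can be neither confirmed nor faulted, and it is not at issue here.

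**Inputs from the article.** 220 children (Participants). Dropout from Power analyses: "participant compliance of 82% and an additional dropout of 20" per cent, so 220 × 0.80 = 176. Two sites.

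**Assumptions, not in the article.** Equal split (110 or 88 per site), detection by a two-sided 5% test on one variable, and a true shift of d SD.

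**Step 1: chance of missing a true shift.** With n children per site, power ≈ Φ(d·√(n/2) − 1.96), and the miss rate is 1 − power.

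- n = 110, d = 0.3: 0.3 × √55 = 2.225; 2.225 − 1.96 = 0.265; power 0.60, missed 40%.
- n = 110, d = 0.2: 0.2 × √55 = 1.483; 1.483 − 1.96 = −0.477; power 0.32, missed 68%.
- n = 88, d = 0.3: 0.3 × √44 = 1.990; 1.990 − 1.96 = 0.030; power 0.51, missed 49%.
- n = 88, d = 0.2: 0.2 × √44 = 1.327; 1.327 − 1.96 = −0.633; power 0.26, missed 74%.

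The exact t-test gives the same picture: power for d = 0.2 / 0.3 / 0.4 is 0.261 / 0.508 / 0.751 with 88 per site and 0.315 / 0.601 / 0.840 with 110. At d = 0.5 the miss rate falls to 4% (N = 220) or 9% (N = 176). With a 70:30 split and N = 176 it is 77%, 55% and 14% for d = 0.2, 0.3 and 0.5.

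**Step 2: bias if site is always left out.** Suppose there is no true association, within-site SDs are 1, the split is equal, and site shifts predictor and outcome by d each. The site indicator has variance 1/4, so the expected slope is (d²/4) / (1 + d²/4).

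- d = 0.2: 0.0100 / 1.0100 = 0.010.
- d = 0.3: 0.0225 / 1.0225 = 0.022.

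**Step 3: bias under the conditional rule.** Miss rate times this slope is a rough ceiling: for d = 0.3 and N = 176, 0.488 × 0.022 = 0.011. The actual bias is lower, because the samples in which the shift is missed are those where the observed difference happens to be small. Simulation (6,000 runs per setting, 5% pre-test on the outcome) gives:

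| N | d | Slope: never / pre-test / always adjusted | Type I error: never / pre-test / always |
|---|---|---|---|
| 220 | 0.2 | 0.0107 / 0.0049 / 0.0005 | 0.056 / 0.054 / 0.051 |
| 220 | 0.3 | 0.0209 / 0.0040 / −0.0011 | 0.060 / 0.051 / 0.050 |
| 176 | 0.2 | 0.0093 / 0.0043 / −0.0007 | 0.052 / 0.053 / 0.053 |
| 176 | 0.3 | 0.0209 / 0.0051 / −0.0013 | 0.054 / 0.052 / 0.051 |

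Simulation error is about 0.001 for the slopes and 0.003 for the error rates. If the predictor differs by 0.8 SD between sites and the outcome by 0.3 SD, the pre-test leaves a bias of 0.012 to 0.015 (20,000 runs). Over all the settings tried with outcome shifts of 0.2 to 0.3 SD, the residual bias is about 0.003 to 0.016, with type I error near 5%.

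**Step 4: cost of always adjusting.** For r = 0.3, losing one degree of freedom moves power from 0.9953 to 0.9952 (N = 220) and from 0.9826 to 0.9821 (N = 176).

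**The case against.** Several objections carry weight.

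- **The harm is small.** Large shifts would usually be found, and the small ones that escape do little damage. In the simulation type I error under the pre-test lies in the same range as under constant adjustment (0.049 to 0.055 for d = 0.2 to 0.5). This stands and limits the weight of the point.
- **The 5% test is an assumption.** The preceding sentence of the plan uses fit indices, not p-values. This stands. If several variables are compared and any one difference triggers adjustment, missing all of them is less likely than missing one, so the rates in Step 1 need not equal the chance that site is omitted.
- **An article may leave detection criteria to the full plan.** True, but the conditional rule itself is stated here, and a sharper criterion would not make it a better rule than constant inclusion.
- **Procedures are standardised across sites.** That limits differences in conduct. It does not make the two recruited groups alike.
- **Within-person effects are largely untouched.** If predictors are person-mean centred, which the article does not state, a constant site shift drops out of linear within-person effects. This stands, and the point is limited accordingly.

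A reader might infer three stronger things that the article does not support. One is that a real site shift goes unadjusted about half the time; that holds only near 0.26 to 0.30 SD with equal sites and a 5% test. Another is that site and language are the same factor. Two sites and two languages make this plausible, but no section assigns a language to a site. The third is that the covariate set will differ from outcome to outcome; the wording equally allows one decision for all models.

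**Conclusion.** The point holds as a low-cost improvement and not as a serious flaw. The plan lets the data decide whether to adjust for a fixed design factor that it names as a possible confounder, and gives no criterion. Under an equal split and a two-sided 5% test on one variable, a 0.2 to 0.3 SD shift would be missed in roughly 40 to 75% of cases with 176 to 220 children. The expected consequence is a residual bias of about 0.003 to 0.016 SD per SD in between-person associations, with no material effect on type I error. The miss rates depend on the assumed split, shift and test; the case for constant inclusion does not, because the conditional rule saves only one degree of freedom and keeps some bias that constant adjustment removes.

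**What to change.** Replace the conditional sentence with one such as: site (Lausanne or Basel) is a fixed covariate in every model that estimates a between-person effect, irrespective of any preliminary comparison of the sites. This covers the Aim 1 convergent-validity models, the Aim 2 between-person correlates, and the Aim 3 regressions and diagnosis comparisons. Adding site to the within-person models is harmless but matters little if predictors are person-mean centred. Write the rule into the planned preregistration.

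The cost is one sentence and one degree of freedom per model. Where a predictor differs between sites, its standard error also rises a little: with a 0.3 SD difference and equal sites, site explains 0.0225 / 1.0225 = 2.2% of the predictor's variance, so the standard error grows by a factor of 1/√(1 − 0.022) = 1.011.

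Two refinements are optional. A site-by-predictor interaction could be reported as a sensitivity check. The language-invariance results could be used to decide which items or thresholds to free, since a site intercept cannot correct unequal loadings.
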